#### Credibility and expectancy questionnaire [33]

To measure participants’ expectations about treatment, before the start of the first treatment session participants will respond to the question, “While receiving treatment during the study period, how much do you expect your symptoms to be alleviated?” on a 9-point Likert scale (1 = not at all, 5 = somewhat, 9 = very much).

#### Safety

##### Lab tests

In order to assess participants’ suitability and detect AEs, clinical pathology tests for the following variables will be performed before the first treatment session and after the end of the treatment period (week 6): complete blood count, liver function test (including aspartate transaminase, alanine transaminase, and alkaline phosphatase), blood urea nitrogen, creatinine, erythrocyte sedimentation rate, C-reactive protein (CRP), and human chorionic gonadotropin (hCG) (only for women of fertile age). The findings will be recorded in the CRF, and if there are any abnormal results the researcher will decide whether the participant should be taken out of the trial; if necessary, further testing and therapeutic interventions will be performed.

##### Adverse events (AEs)

All AEs will be investigated at each visit and recorded in the CRF; AEs do not need to show a clear causal relationship with the relevant treatment. Serious AEs will also be recorded [34]. Since the patient’s group may be revealed during AE assessment, this will be recorded by a subinvestigator in a separate CRF. All AEs will be classified according to the three-grade classification of Spilker et al. [35]^,^ into Mild (1): not impairing the participant’s normal daily life (or function), causing minimal discomfort, and readily endured; Moderate (2): causing discomfort that interferes significantly with the participant’s normal daily life (or function); or Severe (3): making normal daily life (or function) impossible. The causal relationship of AEs with the procedure will be classified according to the World Health Organization-Uppsala Monitoring Centre (WHO-UMC) causality scale, [34] as (1) definitely related, (2) probably related, (3) possibly related, (4) probably not related, (5) definitely not related, or (6) unknown.

### Sample size

This is an investigator-initiated clinical trial, and we have calculated the required sample size with reference to similar studies and our clinical experience. First, we set a significance level of α = 0.05 (two-tailed tests), a type 2 error (β) of 0.2, and a test power of 80%. Because there are no previous studies comparing pharmacopuncture with PT for the TMJ, we selected a moderate-to-high effect size for the comparison of mean VAS between the two groups based on our clinical experience, and used Cohen’s d = 0.65 [36]. Using these parameters, we calculated the sample size using G*Power 3.1.7. Based on an effect size = 0.65, the required sample size was estimated to be 39 persons/group (total 78 persons). However, as we plan to use an analysis of covariance (ANCOVA) correcting for the outcome at baseline for our main analysis, we calculated the sample size assuming the correlation between baseline and primary endpoint to be 0.4 [(1–0.4*0.4)*78], and found that the minimum required number of participants was a total of 65 persons [37]. Thus, to account for a dropout rate of 20%, we calculated that the number of participants we need to recruit is a total of 82 persons (41 persons/group).

### Patient and public involvement statement

Patients will be involved in recruitment and conduct of the study. We will keep in touch with the patients from recruitment to 6 months after treatment. The patients will be able to contact researchers at any time to get information they need.

### Data collection and management

We will use e-CRFs via the Internet-based Clinical Research and Trial (iCReaT) management system, which is operated by the Korea Centers for Disease Control and Prevention. An investigator from the coordinating centre will distribute a standard operating procedure (SOP) to be used in trial processes such as CRF completion and data input and will provide instruction for assessors and investigators at each centre. CRF data will use double data entry, and data entry will be performed by each participating centre and the coordinating centre. After cross-checking the input data, access to the data will be blocked from all investigators except the data coordinator.

### Statistical analysis

As an RCT of chronic TMD patients, this study will compare the difference within and between groups for data on efficacy, safety, and economics. The main analysis will be the ITT analysis, and a PP analysis will also be performed. The demographic results, such as sex, age, occupation, and disease history, and the treatment expectancy will be assessed by group; continuous variables will be presented as the mean ± standard deviation (SD) and categorical variables will be presented as n (%). Differences will be tested using chi-square tests and independent *t* tests. Efficacy outcomes are the changes in continuous outcomes (VAS, NRS, K-BDI, JFLS, EQ5D-5 L, SF-12) at each time point relative to baseline. The primary outcome is the change in VAS from baseline to the primary end point (week 6) in each group. For safety outcomes, we will compare the incidence of AEs between groups; after graphing all the reported ARs in participants who have received treatment at least once, we will calculate the proportion of patients who have experienced AEs in each group, and compare these using chi-square tests and Fisher’s exact test. To compare the HPP and usual care groups, for continuous variables, we will perform an ANCOVA adjusted for the baseline outcome. For categorical variables, we will use chi-square tests of Fisher’s exact test, and to analyse within-group differences between time points, we will use paired *t* tests. Additionally, we will perform an ANCOVA adjusted for baseline outcomes and covariant factors that show a statistically significant difference between the treatment groups at baseline, and we will perform a repeated measures analysis of variance (RM ANOVA) to test differences in the changes across each visit. We will perform subgroup analyses according to RDC/TMD diagnosis (Group Ia, Ib), mouth opening, and K-BDI score. Missing values will be handled in a blinded state, mainly using multiple imputation (MI), last observation carried forward (LOCF) will additionally be used, and sensitivity analyses will be performed. All statistical analysis will be performed using SAS version 9.4 statistical package (SAS Institute, Cary, NC, USA), and statistical significance will be defined as *p* < 0.05.

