### Randomisation and allocation concealment

An independent statistics expert will use nQuery Advisior 7.0 (or SAS 9.0 [SAS Institute Inc., Cary, NC, USA] or SPSS 21.0 [IBM Corp., Armonk, NY, USA]) to allocate participants into each group by block randomisation in a 1:1 ratio (41 persons/group). The results of random allocation will be sealed, such that they cannot be seen from outside, and sent to each centre, where they will be managed in a double-locked container. Before treatment, a random envelope will be opened in front of the enrolled participant, the random allocation numbers assigned to each group will be recorded in an electronic chart, and no changes will be allowed after allocation. Participant enrolment at each centre will proceed by competitive enrolment.

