### Interventions

At both centres, treatment will be administered by a physician who has received prior training in a standardised protocol.

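### The main ANCOVA adjusts for baseline outcome only, so any between-centre difference in week-6 VAS stays in the error term; adding centre would cost one degree of freedom

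*Protocol article*

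**What the plan says.** All references are to the protocol article.

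- *Study design and setting*: two hospitals take part.
- *Randomisation and allocation concealment*: blocked 1:1 allocation, 41 per group. The sealed allocations are "sent to each centre, where they will be managed in a double-locked container". Then: "Participant enrolment at each centre will proceed by competitive enrolment". The section does not say whether the blocks are generated separately for each centre.
- *Statistical analysis*: "for continuous variables, we will perform an ANCOVA adjusted for the baseline outcome". An additional ANCOVA may take in further covariates, but only those that differ significantly between the groups at baseline. Centre is not named as a covariate, a stratum or a subgroup.
- *Sample size*: ANCOVA correcting for the baseline outcome is called the main analysis, and the trial is sized on it.
- *Interventions*: "At both centres, treatment will be administered by a physician who has received prior training in a standardised protocol".

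**The concern.** The covariate set of the main model is stated, and the Sample size section relies on it. This is therefore a choice that the article makes, not a detail it leaves to an analysis plan.

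Where two centres differ in week-6 pain beyond what baseline pain explains, a model without centre counts that difference as noise. The standard error is then larger than it needs to be. If allocation is also balanced within centre, the treatment contrast carries no between-centre variance but its standard error does, so the test rejects less often than its nominal 5%.

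The route by which other covariates can enter does not solve this. Centre would join the additional ANCOVA only if the arms happened to differ significantly by centre. It would stay out whenever the arms are balanced within centre, which is when leaving it out overstates the standard error most clearly. At stake are a few points of power in a trial sized with little to spare.

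**Working it through.** **1. The plan's own figure.** The Sample size section uses two-sided α = 0.05, 80% power and an effect size given as "used Cohen’s d = 0.65". By the noncentral t distribution, 39 per group gives 80.9% power and 38 gives 79.9%, so 39 per group (78 in total) reproduces. The ANCOVA factor is 1 − 0.4² = 0.84, and 0.84 × 78 = 65.52, stated as 65. With 20% dropout, 65 / 0.8 = 81.25, rounded up to 82. The sample size is right on its own inputs. Below, 65.52 is rounded up to 66 evaluable, 33 per arm.

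**2. Set-up.** Scale week-6 VAS to SD 1 within centre. After baseline adjustment the residual variance is 0.84. Let the centres differ by D at week 6 with no matching difference at baseline. For two equal centres the between-centre variance is D²/4, and its share of the residual is f = (D²/4) / (0.84 + D²/4). D is an assumption, because the document gives no figure for it.

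- D = 0.2: 0.01 / 0.85 = 1.2%
- D = 0.4: 0.04 / 0.88 = 4.5%
- D = 0.6: 0.09 / 0.93 = 9.7%
- D = 0.8: 0.16 / 1.00 = 16%

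**3. Power with centre in the model.** Noncentrality = (0.65 / √0.84) × √(33 × 33 / 66) = 0.709 × 4.062 = 2.88. With 62 degrees of freedom this gives 80.95%. When D = 0, the model without centre (63 degrees of freedom) gives 80.97%, so the extra degree of freedom costs 0.02 points.

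**4. Without centre, arms balanced within centre.** The estimate keeps the same sampling variance, but its standard error is inflated by 1/√(1 − f). This is the same as raising the critical value of 1.998 to 1.998/√(1 − f).

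| D (SD) | Effective critical value | Type I error | Power | Loss against 80.95% (points) |
|---|---|---|---|---|
| 0.2 | 2.010 | 4.9% | 80.7% | 0.3 |
| 0.4 | 2.045 | 4.5% | 79.7% | 1.3 |
| 0.6 | 2.103 | 4.0% | 78.0% | 2.9 |
| 0.8 | 2.180 | 3.3% | 75.7% | 5.3 |

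Simulation of the same setting (8,000 runs per cell) agrees:

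| D (SD) | Without centre: type I error, power | With centre: type I error, power |
|---|---|---|
| 0.4 | 4.7%, 79.0% | 5.3%, 80.5% |
| 0.6 | 3.8%, 77.4% | 4.9%, 80.8% |
| 0.8 | 3.1%, 74.7% | 4.9%, 80.2% |

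At 0.2 SD the simulated powers were 80.0% without centre and 80.4% with it.

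**5. Without centre, allocation not stratified by centre.** The estimate itself now carries the between-centre variance, so the standard error is honest. Simulated type I error, with a 65:35 centre split, was 5.3%, 4.8% and 4.9% at f = 5%, 10% and 20%. Only precision is lost. With d = 0.65 taken on the within-centre SD, power for 66 evaluable is 79.0%, 76.8% and 71.8% at those shares, against about 81% with no centre difference.

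**The case against.** Several points on the other side are sound.

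- **Stratification is not documented.** Envelopes sent to each centre suggest separate lists, but one sequence divided between the sites would fit the same words. A reader might infer that the type I error is certainly off its nominal level. The text does not support that: it holds only if blocks are separate by centre, and even then the error is towards too few rejections.
- **Confounding by centre.** A reader might infer that the treatment estimate is biased if the arms are uneven across centres. Allocation is randomised, so any such imbalance is chance, and the standard error already allows for it.
- **Size.** The larger losses need a centre difference of 0.6 to 0.8 SD, close to or above the planned treatment effect, and nothing in the document points to one that large. The shared training, the standardised injection method and the common TENS device all work against it.
- **Baseline adjustment already helps.** If the centres differ by 0.6 SD at baseline as well as at week 6, simulated power is 79.1% without centre against 80.1% with it.
- **Unequal recruitment makes it milder.** At 0.6 SD, an 80:20 centre split gives 77.7% against 79.8%, while equal centres give 76.3% against 79.8%. Competitive enrolment is therefore not an aggravating factor for the loss of power.

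These points limit the size and remove any claim of bias. They do not give a reason to leave centre out: the model is stated, centre is known for every participant, and including it costs almost nothing when the centres do not differ.

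**Conclusion.** The point holds as one of efficiency, with a possible loss of exactness in the test. As written, the main ANCOVA leaves any centre difference not explained by baseline in the error term. With 33 evaluable per arm, d = 0.65, a correlation of 0.4 and two equal centres with arms balanced within them, the loss runs from under 1 point of power at 0.2 SD to about 5 points at 0.8 SD. It can be somewhat larger if allocation is not balanced within centre. The centre difference is assumed throughout, and the range starts at zero.

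The type I error falls below 5% only if blocks are separate by centre. False positives are not inflated in either case, and the treatment estimate is not systematically biased. Nor does this make the figure of 82 wrong. The ANCOVA reduction to 65 evaluable does leave little room above 80% power, so a loss of even 2 or 3 points would take the trial below its own target.

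**What to change.** In the Statistical analysis section, define the primary model as an ANCOVA of week-6 VAS change on treatment, baseline VAS and centre (fixed effect, two levels). Use the same covariates in the other ANCOVAs for consistency. Centre should be prespecified and not made to depend on a baseline significance test.

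It would also help to say in the Randomisation and allocation concealment section whether the blocks are generated separately for each centre, since that decides whether centre is needed for an exact type I error or only for precision.

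The cost is one model term and one degree of freedom: 80.97% to 80.95% power if the centres do not differ at all. The sample size need not change.

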**Assessments**											
Symptoms and change in medicine			○	○	○	○	○	○	○	○	○
NRS of TMJ pain/Bothersomeness			← Every visit →					○	○	○	○
VAS of TMJ pain	○		○	○	○	○	○	○	○	○	○
K-BDI-II			○					○		○	○
JFLS			○					○		○	○
TMJ range of motion (maximum mouth opening, mandibular excursive movement)	○		○	○	○	○	○	○	○	○	○
Compliance				○	○	○	○	○			
PGIC								○			○
EQ-5D-5 L			○			○		○	○	○	○
SF-12			○			○		○	○	○	○
Credibility and expectancy			○								
Adverse events			← Every visit →					○	○	○	○

*EQ-5D-5 L* EuroQol-5 Dimension-5 Level; *HPP* hominis placental pharmacopuncture, *NRS* Numeric Rating Scale; *PGIC* Patient Global Impression of Change; *RDC/TMD* Research Diagnostic Criteria for Temporomandibular Disorders; *PT* physical therapy; *SF-12* Short Form Health Survey 12; *TENS* Transcutaneous Electrical Nerve Stimulation; *TMJ* temporomandibular joint; *VAS* Visual Analogue Scale

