Nevertheless, our study also has some limitations. First, the study design makes it impossible to blind participants and physicians. However, the physicians and assessors were separated; the assessors did not participate in treatment procedures, performed assessments in a separate space, and were thoroughly blinded to group allocation. Second, psychiatric and psychological factors are known to be important predictive factors for therapeutic effect in TMD [58], but we will not match these factors in the screening stage. This is to minimise selection bias, and, to minimise the effects of these psychiatric and psychological factors, group allocation will be randomised, and we will perform subgroup analysis by K-BDI score to investigate the effects of these factors. Third, because this study includes long-term follow-up, it could be difficult to maintain compliance during follow-up. Accordingly, we will make efforts to improve compliance, such as regular phone calls to participants.

We hope the data from this study will contribute to evidentiary data for standard Korean medicine clinical treatment guidelines. In addition, the study design and methodology can be used as a reference for future clinical trials of acute and subacute TMD or other musculoskeletal disease, as well as studies of other types of pharmacopuncture.

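### The additional ANCOVA picks its covariates by baseline significance tests, and the tested list includes treatment expectancy, which may be recorded after the participant knows the allocation

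*Protocol article*

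**What the plan says.** The Statistical analysis section gives the main between-group comparison of continuous outcomes first: "we will perform an ANCOVA adjusted for the baseline outcome". The Sample size section likewise names a baseline-adjusted ANCOVA as the main analysis. A second, additional ANCOVA is then announced, adjusted for the baseline outcome and for "covariant factors that show a statistically significant difference between the treatment groups at baseline".

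The factors compared between arms are introduced by example: sex, age, occupation and disease history, "and the treatment expectancy will be assessed by group". The section then says "Differences will be tested using chi-square tests and independent" t tests, and "statistical significance will be defined as" p < 0.05. Nothing exempts expectancy from the covariate rule.

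On timing, the section on the expectancy questionnaire says that "before the start of the first treatment session participants will respond to the question". In Table 1 the row "Credibility and expectancy" is marked only in the Week 1 column, which stands under the heading for treatment after allocation; random allocation is marked at Week 0. The Study design section puts allocation and first treatment at the second visit. The Randomisation section has the envelope opened in front of the participant before treatment, and the Blinding section describes an open-label trial in which only the assessor is blinded.

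**The concern.** There are two faults in the rule.

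First, if randomisation is sound, any significant difference in a factor fixed before allocation is a chance event. Its p-value measures imbalance, not prognostic value. The rule can bring in a factor unrelated to week-6 VAS and leave out a strong predictor that happens to be balanced. The model for the additional analysis is unknown until the arms have been compared.

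Second, expectancy may not be a baseline factor at all. If participants answer after seeing their allocation, a difference between arms in expectancy can be a result of the allocation. Adjusting for it then removes whatever part of the treatment effect runs through expectancy, and the adjusted coefficient no longer estimates the same quantity as the main ANCOVA. The rule makes this worse, because it selects expectancy most often when allocation has shifted it most. The trial could then report two ANCOVA results for its primary outcome that disagree for a reason unrelated to prognostic imbalance.

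**Working it through.** **The plan's own figure.** A two-sample t test with d = 0.65, two-sided α = 0.05 and 80% power needs 38.14, so 39 per group and 78 in total. The ANCOVA factor gives (1 − 0.4²) × 78 = 65.52, stated as 65. Allowing for 20% dropout, 65 / 0.8 = 81.25, so 82. The stated 82 is reproduced, and nothing below changes it.

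**Spurious selection.** For k independent tests at 0.05 with no true difference, P(at least one significant) = 1 − 0.95^k.

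- k = 4 (sex, age, occupation, disease history): 1 − 0.95⁴ = 0.185.
- k = 5 (adding expectancy, treated here as a true baseline factor): 1 − 0.95⁵ = 0.226.

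The list is open-ended, so the actual number of tests may be larger. Independence is an assumption.

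**Order of events at Visit 2.** Table 1 lists Visit 2 under both Week 0 and Week 1. The envelope is opened before treatment, and the expectancy question is asked before the first treatment session. Both statements can be true in either order. The Table 1 column points to expectancy coming second, but K-BDI-II, JFLS, EQ-5D-5L and SF-12 also have their first mark in that column and must serve as baseline values. After allocation is therefore the likelier reading for expectancy, but it is not proven.

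**Effect of adjusting for expectancy, if it is asked after allocation.** Let δ be the difference in expectancy between arms (in SD) and b the slope of the outcome on expectancy, given arm and baseline. The documents give neither, so both are assumed. With a total effect of 0.65 SD, the coefficient for arm after adjustment is 0.65 − bδ. For δ = 0.5 and b = 0.3 this is 0.65 − 0.15 = 0.50, a loss of 0.15 / 0.65 = 23%. For δ from 0.3 to 0.8 and b from 0.2 to 0.4, the loss runs from 0.06 / 0.65 = 9% to 0.32 / 0.65 = 49%.

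A simulation (82 participants with no loss, baseline correlation 0.4, 4,000 runs per cell) added expectancy to the model only when its t test gave p < 0.05:

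| Assumed shift δ | Expectancy selected | Mean estimate when selected (b = 0.2 / 0.3 / 0.4) |
|---|---|---|
| 0 | about 5% | 0.66 / 0.63 / 0.65 |
| 0.3 | about 27% | 0.59 / 0.56 / 0.53 |
| 0.5 | about 60% | 0.55 / 0.50 / 0.45 |
| 0.8 | about 95% | 0.49 / 0.41 / 0.34 |

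The ANCOVA on baseline only stayed at about 0.65 in every cell. For δ = 0.5 and b = 0.3, averaging over all trials, selected or not, gives 0.54. The illustration takes the arm with the better outcome to have the higher expectancy; the reverse would move the estimate up by the same amount.

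**The case against.** The strongest defence is that the pre-specified main analysis adjusts for the baseline outcome alone. It does not depend on the data and is not touched by this rule. That stands, and it limits the severity. A reader might infer that the primary result itself is biased; the Sample size and Statistical analysis sections do not support that.

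A reader might also take it as fact that expectancy is recorded after allocation. The documents do not establish this, for the reasons given on the order of events. It remains a real possibility that the plan leaves open.

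Nor is leaving K-BDI-II and centre out of the main ANCOVA an error. The Discussion says that "psychiatric and psychological factors are known to be important predictive factors for therapeutic effect in TMD", but the plan addresses this through a subgroup analysis by K-BDI score, and no stratification by centre is stated. Adjusting for the baseline outcome alone is valid. The documents give no figure for the variance that K-BDI-II would explain, so any gain in precision cannot be sized from them.

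The shifts and slopes are assumptions, and the loss arises only when expectancy is selected. That also stands. The data analyst is unblinded, but a p < 0.05 rule is largely mechanical; the discretion lies in the open-ended list of factors.

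What the defence does not answer is the rule itself. It is stated in the text, so it is not a detail left to an analysis plan, and it lets in expectancy without any condition on when it was recorded.

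**Conclusion.** The point holds for the additional ANCOVA only, and should be fixed. Choosing covariates by between-arm significance is unsound in a randomised trial whatever the timing of expectancy. With the factors named, it brings in at least one chance covariate about 19% to 23% of the time, assuming independent tests.

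The harm from expectancy is conditional. It requires that expectancy is recorded once allocation is known, differs by arm, affects VAS and passes the significance test. Under the assumed 0.5 SD shift and slope of 0.3, the adjusted estimate drops from 0.65 to 0.50 SD in the roughly 60% of trials where expectancy is selected. With no shift it is selected about 5% of the time and there is essentially no bias. The main ANCOVA and the sample size of 82 stand.

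**What to change.** 1. Delete the significance-based rule for choosing covariates.
2. Name the additional ANCOVA's covariates in advance from variables fixed before randomisation: baseline VAS, centre, and any other prognostic factors recorded at screening. Keep them whatever imbalance is seen. Table 1 marks VAS at screening, so a reading before randomisation exists.
3. Use K-BDI-II as a covariate only if it is recorded before the envelope is opened. Table 1 first marks it in the same column as expectancy, so the schedule should state the order.
4. State in the same way whether expectancy is asked before or after the envelope is opened. Unless it is collected before allocation is revealed, keep it out of the adjusted effect estimate and report it descriptively or as exploratory.

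The cost is wording in the analysis section and the schedule, plus one or two model degrees of freedom. If K-BDI-II or expectancy is to be used as a covariate and is now taken after allocation, it must also be moved earlier within Visit 2. The sample size does not change.

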### Participants schedule

The specific participant schedule is shown in Table 1.

**Table 1 Tab1:** Participants schedule

	Study period										
Time point	Screening	Enrollment, Allocation	Active treatment after allocation					Follow-up			
	Week − 1	Week 0 (Baseline)	Week	Week	Week	Week	Week	Week	Week	Week	Week
			1	2	3	4	5	6	9	13	25
	Visit 1	Visit 2	Visit 2, 3	Visit 4, 5	Visit 6,7	Visit 8,9	Visit 10,11	Visit 12	Visit 13	Visit 14	Visit 15
Window period			±3	±3	±3	±3	±3	±3	±14	±14	±14

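### The additional trajectory test (RM ANOVA), LOCF and the within-arm paired t tests are weak choices for secondary and sensitivity analyses; a mixed model and delta-adjusted imputation would serve better with no new data

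*Protocol article*

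**What the plan says.** The Statistical analysis section of the protocol article makes ITT the main analysis and compares the groups on continuous outcomes by ANCOVA adjusted for the baseline value. The Sample size section also names this ANCOVA as the main analysis. Missing values are handled chiefly by multiple imputation (MI). Three further methods are named in the same section:

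- Trajectory over time: "we will perform a repeated measures analysis of variance (RM ANOVA) to test differences in the changes across each visit". This is introduced as an additional analysis.
- Missing data, after MI: "last observation carried forward (LOCF) will additionally be used, and sensitivity analyses will be performed". The type of sensitivity analysis is not given.
- Change within each arm: "to analyse within-group differences between time points, we will use paired" t tests.

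Table 1 (Participants schedule) has VAS at screening and in the columns for weeks 1, 2, 3, 4, 5, 6, 9, 13 and 25. Under Concomitant treatment, other TMD treatment is restricted up to week 6 and unrestricted afterwards.

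**The concern.** Each of the three methods has a known weakness that bears on this design.

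**RM ANOVA.** The univariate group-by-visit F test is exact only under sphericity. Visits 1 week apart during treatment and up to 12 weeks apart in follow-up, with a change in permitted treatment at week 6, make equal covariances unlikely. The classical procedure also needs a full set of visits from each participant.

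**LOCF.** It is the only named alternative to MI. It freezes pain at the last visit attended and does not vary the missing-at-random (MAR) assumption, so agreement between LOCF and MI is weak reassurance. Participants and providers are unblinded and the arms are injection and TENS, so dropout could differ between arms.

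**Paired t tests.** They test change within an arm, which mixes treatment effect, natural course and regression to the mean after an entry threshold of VAS 40 mm. The article sets one threshold of p < 0.05 and does not label these tests descriptive.

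At stake are the claims about the course of pain up to week 25, the strength of the missing-data check on the primary result, and how within-arm p-values are read.

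**Working it through.** **Inputs from the protocol article.** Two-sided α 0.05 and 80% power; d = 0.65; 39 per group before adjustment; baseline to week-6 correlation 0.4; 20% dropout; 82 in total, 41 per arm; the visit schedule above. The article gives no standard deviation in mm, no correlation between other visits and no dropout by arm. Those are assumptions below and are marked as such.

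**1. The plan's own sample size.** In a two-sample t test with d = 0.65, power is 0.7985 at 38 per group and 0.8089 at 39, so 39 per group (78) reproduces. ANCOVA factor: (1 − 0.4²) × 78 = 65.52, which the article gives as 65. Dropout: 65 / 0.8 = 81.25, so 82. The figure stands, and nothing below changes it.

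**2. RM ANOVA, type I error.** Monte Carlo of the group-by-visit F test with no group difference, 41 per arm, nine time points (weeks 0, 2, 3, 4, 5, 6, 9, 13, 25), 5000 runs:

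| Assumed correlation | Mean estimated epsilon | Uncorrected | Greenhouse-Geisser |
|---|---|---|---|
| Constant 0.4 | 0.90 | 0.046 | 0.041 |
| Decaying, 0.4 over 6 weeks | 0.52 | 0.086 | 0.045 |
| Decaying, 0.7 over 6 weeks | 0.40 | 0.103 | 0.049 |

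Varying this to 33 or 41 per arm and nine or ten time points gave 0.096 to 0.120 under decaying correlation. Overall that is about 9 to 12%.

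**3. RM ANOVA, participants kept.** If run on complete cases at the planned dropout: 82 × 0.8 = 65.6, about 66.

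**4. LOCF, simple arithmetic.** Assume improvements at week 6 of 28 mm (HPP) and 15 mm (PT), a true difference of 13 mm, linear over time. Assume the last visit before dropout is spread evenly over weeks 1 to 5. A dropout then contributes on average (1 + 2 + 3 + 4 + 5) / 5 / 6 = 0.5 of the full improvement.

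- 20% in both arms: 13 × (0.8 + 0.2 × 0.5) = 13 × 0.9 = 11.7 mm
- 30% HPP, 10% PT: 28 × 0.85 − 15 × 0.95 = 23.80 − 14.25 = 9.55 mm
- 10% HPP, 30% PT: 28 × 0.95 − 15 × 0.85 = 26.60 − 12.75 = 13.85 mm

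**5. LOCF, type I error.** Monte Carlo of week-6 ANCOVA, 41 per arm, 3000 runs. Assumptions: both arms improve by 1 SD over 6 weeks, and dropout depends on observed pain (MAR). Negative values favour HPP; 30%/10% means 30% in the comparator and 10% in HPP.

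| Dropout | True effect (SD) | LOCF estimate | LOCF rejection rate | MAR likelihood-type estimate |
|---|---|---|---|---|
| 20%/20% | 0 | 0.001 | 0.049 | 0.006 |
| 30%/10% | 0 | −0.170 | 0.123 | 0.000 |
| 20%/20% | −0.65 | −0.606 | 0.743 | −0.645 |
| 30%/10% | −0.65 | −0.804 | 0.939 | −0.647 |

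The last column stands in for a mixed model; MI under MAR targets the same quantity. By symmetry, the null bias reverses sign if the higher dropout is in the HPP arm.

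**6. Paired t tests.** Suppose both arms improve equally, with 41 per arm and r = 0.4. If p is the chance that one arm is significant, exactly one arm is significant with probability 2p(1 − p). For assumed improvements of 0.2, 0.35, 0.5 and 0.8 SD, p is 0.207, 0.515, 0.814 and 0.995, and the probability is 0.33, 0.50, 0.30 and 0.01. A contrast of significant in one arm against not significant in the other would therefore often appear with no difference between treatments.

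**The case against.** The strongest objection is that none of this reaches the trial's main conclusion. It is right. The week-6 comparison is a baseline-adjusted ANCOVA under ITT with mainly MI, and RM ANOVA and LOCF are both described as additional. Efficacy outcomes are changes at each time point and the ANCOVA applies to continuous outcomes, so adjusted comparisons at weeks 9, 13 and 25 are already covered. A mixed model is itself MAR-based and adds little over ANCOVA with MI at week 6. A reader might infer that the primary result is compromised; the article does not support that.

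Other stronger readings also fail:

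- **That the RM ANOVA will have inflated error.** The inflation needs decaying correlation and no correction. Under constant correlation the rate is 0.046, and Greenhouse-Geisser restores about 5%. The article neither states nor excludes a correction.
- **That incomplete participants will be dropped.** No section says so, and RM ANOVA could be run on imputed data. A loss to about 50 of 82 arises only with an assumed 3% intermittent missingness at each of nine visits (82 × 0.8 × 0.97⁹ = 49.9), a rate that is not in the article.
- **That LOCF generally inflates error.** With equal dropout the type I error is 0.049 and the effect is slightly diluted.
- **That departures from MAR will go unexamined.** Further sensitivity analyses are promised. Their content is commonly left to the full protocol or SAP, so its absence is no error.
- **That the paired t tests are the efficacy test.** The between-group question is given to ANCOVA. The size of regression to the mean depends on which VAS serves as baseline and on assumed means and correlations, so no figure is claimed for it here.

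What remains is that three weaker methods are named where better ones are available for the same data.

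**Conclusion.** The concern holds for the secondary and sensitivity analyses only, and is minor to moderate. The sample size of 82 and the primary analysis stand.

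- The RM ANOVA trajectory test carries about 9 to 12% type I error if correlation decays with time and no correction is applied. It would keep about 66 of 82 if restricted to complete cases.
- LOCF is a poor check on MI. It leaves the MAR assumption untested and is biased when dropout differs by arm (type I error about 12% at an assumed 30%/10%), and mildly conservative when dropout is equal.
- Within-arm paired t tests cannot support a statement about HPP versus PT.

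The correlation structures, the improvement sizes and the dropout by arm are assumptions. Only r = 0.4 between baseline and week 6 and 20% overall dropout come from the article.

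**What to change.** Before the data are analysed:

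1. Replace the additional RM ANOVA by a mixed model for repeated measures with baseline value, centre, group, visit and group-by-visit. Use all observed visits and report HPP − PT contrasts with confidence intervals at weeks 6, 9, 13 and 25. Specify an unstructured covariance and an ordered, simpler fallback. Nine visits would need 9 × 10 / 2 = 45 covariance parameters from 82 participants, and the analyst is not blinded, so the fallback should be fixed in advance.
2. Keep ANCOVA with MI as the primary analysis. Replace LOCF by delta-adjusted (tipping-point) MI as its sensitivity analysis, with the shifts allowed to differ by arm.
3. Report within-arm changes as means with confidence intervals, labelled descriptive, without paired tests.

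The cost is a change of wording and modest programming in the SAS 9.4 already named. No new data or participants are needed. The downside is that the unstructured covariance may not converge at this sample size, so the fallback may have to be used.
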